## Description of the methodology

### Design

This study will follow a type 2 hybrid design (26) to implement and evaluate a complex intervention, using mixed methods. In detail, we will conduct a single centre, pragmatic, stepped-wedge randomized cluster open-label trial design (27). The units of randomization will be five geriatric rehabilitation units of the ICH (5 clusters). The unit of analysis will be the patient.

All clusters (hospital wards) will begin the study under the control condition. Subsequently, they will be randomly assigned to the intervention at predetermined time points in a sequential, staggered manner until all clusters receive the intervention (see Figure 1).

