### Outcomes

The primary outcome of the study is the mean number of medications per patient.

Secondary outcomes are (see also “Participant timeline and data collection”): prevalence of quantitative polypharmacy and hyperpolypharmacy, qualitative polypharmacy, PIMs, anticholinergic burden, number of underprescribed medications that have been started, ADEs and adverse drug withdrawal events (ADWEs), unplanned care utilization, and mortality. Patient-reported outcome measures (PROMs) will also be secondary outcomes for this study. They include adherence, treatment burden, perceived health status and quality of life, health literacy, and attitudes on deprescription (see Table 1). Finally, another secondary outcome will be the identification of barriers and facilitators of the implementation of the purposed methodology, both at the level of the individual person/healthcare professionals (possible cultural aspects, preferences, etc.) as well as from the system point of view (aspects related to intermediate care).

**Table 1 tab1:** Detailed collected variables.

Demographic variables	Multidimensional assessment	Medication assessment	PROMs

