### Sample size and recruitment

Sample size was calculated using the Stata command stepped-wedge, considering 5 clusters, a size of each cluster *N* = 10 and five times of measurement after baseline, incorporating one cluster to the intervention phase at each time. Based on previous studies (21), taking a baseline mean drugs of 8.81 and expected decrease of 1.31, we considered an ICC = 0.2 (intraclass correlation). With this data, a sample size of 300 subjects will provide a power of 75%. The sample size was calculated by a statistician within the research group.

For the qualitative part, we aim to recruit and interview 15 older patients with different frailty profiles (mild, moderate, and severe frailty), from both genders. Caregivers of those patients, especially the most severely frail, and 5 geriatricians will also be invited to join the study. We estimate a total of 20–30 participants in this group. Additionally, we aim to include a minimum of 4 focal participation groups (between 5 and 10 people per group), including both patients and healthcare professionals (geriatricians, pharmacists and nurses). The selection of the group participants will be performed to obtain a balanced representation of the different profiles.

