### Data analysis

Baseline variables will be described using means and standard deviations for quantitative variables and absolute and relative frequencies for categorical variables, with their corresponding 95% confidence intervals. The Student’s t-test will be used to compare means of medications and other qualitative variables, and the chi-squared test will be used to compare polypharmacy, hyperpolypharmacy, ADEs, ADWEs, and other categorical variables. All analyses will be stratified according to frailty and to age groups, as appropriate.

We will perform a generalized lineal model with mixed effects for (individual) time and cluster. In the descriptive analysis we also will perform descriptions for each cluster. The ICC for within-cluster correlation will be analyzed and recalculated with the data result and included in a sensitivity analysis.

Multivariable analyses will be carried out to assess the association between decrease in the number of medications at discharge and possible determinants. PROMs will be assessed by comparison of scores before and after the intervention by using paired t-test for continuous variables and McNemar’s test for categorical variables. Cox proportional hazard models will be used to evaluate the association between intervention and survival or time to first unplanned health care utilization. Missing data will be handled according to multivariate imputations by chained equations. Interim analyses are not planned.

All the analysis of secondary outcomes will only be exploratory as far as the sample size is not powered to detect differences on these variables.

All analyses will be carried out according to the intention-to-treat principle, with statistical significance at *p* < 0.05. STATA and R-Studio software will be used in their most recent versions available for statistical analysis.

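### The primary outcome is assigned a t-test that ignores ward and calendar step, and the plan does not say whether that test or the unassigned mixed model decides; if the t-test decides, the false-positive rate is about 30% at ICC 0.2

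*Protocol article*

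**What the plan says.** All places are in the Protocol article.

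- Outcomes: "The primary outcome of the study is the mean number of medications per patient".
- Data analysis, first paragraph: a Student's "t-test will be used to compare means of medications and other qualitative variables, and the chi-squared test will be used to compare polypharmacy". The list for the second test reads in full: "chi-squared test will be used to compare polypharmacy, hyperpolypharmacy, ADEs, ADWEs, and other categorical variables".
- Data analysis, second paragraph: "We will perform a generalized lineal model with mixed effects for (individual) time and cluster". No outcome is named in that sentence. The paragraph also plans descriptions by cluster and a sensitivity analysis with the ICC re-estimated from the data.
- Data analysis, closing paragraphs: "All the analysis of secondary outcomes will only be exploratory", and all analyses are by intention to treat, "with statistical significance at *p* < 0.05".
- Design, Figure 1 legend, and Sample size and recruitment: five wards are randomised, with a baseline period and five steps, one ward crossing over at each step, 10 patients per ward and period, an ICC of 0.2, and 300 patients for 75% power.

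**The concern.** In a stepped-wedge trial the treatment contrast is entangled with ward and with calendar time. The wards do not contribute equally to the two phases: the first to cross over supplies 10 control and 50 intervention patients, the last supplies 50 and 10. A two-sample t-test or a chi-squared test on the pooled patients treats all 300 as independent. Differences between wards, and any drift in prescribing over the study, then pass into the apparent effect.

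The sentence cannot be confined to a baseline table, because it includes ADEs and ADWEs, which are counted only after enrolment (Participant timeline and data collection). The same sentence names the mean medication count, which is the primary outcome.

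What is at stake is which result the trial reports. One named test suits the design and one does not. The unsuitable one is tied by name to the primary outcome, and the suitable one is tied to nothing. The 75% power comes from a stepped-wedge calculation and does not describe a t-test.

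**Working it through.** **The plan's own figure.** 5 wards × 6 periods × 10 patients = 300, which agrees. The SD of the medication count is not stated, so the 75% power can be neither confirmed nor refuted. Under the Hussey-Hughes variance (two-sided 5%, ICC 0.2, decrease of 1.31) it corresponds to a total SD of about 2.74. The type I error below does not need the SD, because it cancels.

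**Layout.** In order of crossover, the wards give 50, 40, 30, 20 and 10 intervention patients and 10, 20, 30, 40 and 50 control patients: 150 in each phase.

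**Variance of the crude phase difference**, in units of the total variance, with a random ward intercept and ICC ρ:

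- Net weight of each ward = (intervention − control)/150 = +40, +20, 0, −20, −40, each over 150.
- Sum of squared weights = (1600 + 400 + 0 + 400 + 1600)/22,500 = 0.1778.
- True variance = 0.1778ρ + (1 − ρ) × 2/150. At ρ = 0.2 this is 0.0356 + 0.0107 = 0.0462.
- Variance assumed by the t-test = 2/150 = 0.0133.
- Ratio = 0.0462/0.0133 = 3.47.

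**Type I error of the t-test on the medication count**, two-sided 5% (sidedness is not stated; two-sided is assumed): 2 × [1 − Φ(1.96/√3.47)] = 2 × [1 − Φ(1.053)] = 0.29. Simulation of 40,000 trials per scenario, with no effect and no calendar trend:

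| ICC | Variance ratio | Analytic error | Simulated error |
|---|---|---|---|
| 0.01 | 1.12 | 6.4% | 6.6% |
| 0.05 | 1.62 | 12.3% | 12.4% |
| 0.10 | 2.23 | 19.0% | 19.2% |
| 0.20 (the plan's value) | 3.47 | 29.2% | 30.6% |

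**Calendar time.** Numbering the periods 1 to 6, control patients enrol on average in period (5×1 + 4×2 + 3×3 + 2×4 + 1×5)/15 = 2.33, and intervention patients in period (1×2 + 2×3 + 3×4 + 4×5 + 5×6)/15 = 4.67. A drift of d per period therefore shifts the crude difference by 2.33d. The documents give no drift. With an assumed 0.05 or 0.1 SD per period at ICC 0.2, the simulated error is 37% or 54%.

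**Chi-squared for the binary outcomes.** No ICC is stated for them. In beta-binomial simulations with event rates of 10% to 80%, the error is 12% to 13% at an assumed ICC of 0.05 and 26% to 32% at an assumed 0.2.

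**With ward and step in the analysis.** Fixed ward and step effects give 4.8% (20,000 trials, ICC 0.2, drift of 0.1 SD per period). A random-ward mixed model with period effects gave 5.0%, but in only 400 trials, without drift and with some convergence warnings, so that second figure is only indicative.

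**The case against.** The plan does contain a model with time and cluster effects, and it re-estimates the ICC. The sample size was computed for a stepped wedge. A sensible reading is that the t-test and chi-squared test are crude first looks and that the model decides. The sentence on these tests directly follows the one on describing baseline variables, it never says that phases are what is compared, and medication count and polypharmacy are also measured on admission. The choice of a primary model and the model form for each secondary outcome are often left to a statistical analysis plan.

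Much of this stands, and it rules out three stronger readings.

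- A reader might infer that the trial as planned has a 30% false-positive rate. The documents do not support that: the figure belongs to the t-test, and only if it decides the result.
- A reader might infer that chi-squared is the only analysis planned for polypharmacy, ADEs and ADWEs. The model is generalized, so it can take binary outcomes, and no outcome is excluded from it.
- A reader might carry the ICC of 0.2 over to those outcomes, or treat the statement "The unit of analysis will be the patient" as an error. The ICC was given for the medication count only, the secondary outcomes are declared exploratory, and patient-level analysis is sound when ward is in the model.

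What does not stand is the reading as a baseline table, because ADEs and ADWEs cannot be baseline variables. Comparison of control with intervention is an inference, but the natural one for a list of outcomes. Nor is this only detail left to another document: the article names a test for the primary outcome that does not fit its design and sets beside it a model whose role it leaves open.

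**Conclusion.** The point holds in conditional form. The Data analysis section assigns the primary outcome a test that ignores ward and step, plans a more suitable model without an outcome, and does not say which governs at the 5% level. If the t-test governs, its false-positive rate for the medication count is about 30% (29% analytic, 31% simulated). That rests on the plan's ICC of 0.2, equal cells of 10, a constant ward effect, a two-sided test and no calendar trend. A smaller ICC reduces it, to about 12% at 0.05. A calendar trend would raise it, but no trend is documented.

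For the binary outcomes the chi-squared p-values would also be too small, by an amount that depends on an unstated ICC. Their exploratory status lowers the consequence without making the test valid. This should be corrected before analysis, because the primary inference is at stake and the remedy is cheap.

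**What to change.** Rewrite the first two paragraphs of Data analysis:

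- Name the mixed model with treatment, calendar-step and ward terms, with a small-sample correction for five wards, as the sole test of the medication count.
- Use its binary counterpart for polypharmacy, hyperpolypharmacy, ADEs and ADWEs, still labelled exploratory.
- Keep crude summaries by phase, ward and step as description, without t-test or chi-squared p-values for outcomes.
- Correct 'qualitative' to 'quantitative' where the t-test's variables are listed; it is an evident slip.

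The cost is one paragraph of wording. No further patients or data are needed. Confidence intervals will be wider than the crude tests would give.

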### Study setting

The study will be developed in an urban ICH “Parc Sanitari Pere Virgili,” Barcelona, Spain. The facility includes 360 inpatient beds, divided into geriatric rehabilitation, subacute care, palliative care, and long-term care, and approximately 40 hospital-at-home beds.

Patients will be included from the five geriatric rehabilitation wards. Most of the admitted patients usually come from a hip fracture or a stroke, or they are admitted following a stay in an acute care ward. The medical staff consists of geriatricians and general practitioners, and multidisciplinary team includes nurses, pharmacists, physiotherapists, occupational therapists, psychologists and social workers, among others. The average length of stay per patient is around 30 days.

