**Figure 3 fig3:**
[figure not shown]
Timeline of included subjects. ADEs, adverse drug events; ADWEs, adverse drug withdrawal events; PROMs, patient-reported outcome measures.

In both intervention and control phase, ADEs/ADWEs will be identified by research staff based on a retrospective review of medical records from enrolment to index hospital discharge, or 30 days post recruitment, whatever comes first (post-intervention assessment). We will apply systematic trigger tools suggestive of ADEs/ADWEs occurrence (see Table 2). In detail, the final list is derived from the integration of different validated trigger tools that have been previously used in similar populations. The list was reviewed and validated by geriatricians and pharmacists within the research team (30–32).

**Table 2 tab2:** List of possible “alerts” for ADEs/ADWEs.

Type	Alert
Care alerts	Transfusion or use of blood products
	Code / arrest / rapid response team
	Acute dialysis / Acute kidney injury
	X-ray or Doppler studies for embolism or deep vein thrombosis
	Patient fall
	Immobilization
	In-hospital stroke
	Constipation
	Hypotension
	Lethargy
	Rash
	Unspecified adverse event
	Symptomatic bradycardia
	Delirium
Antidots and treatments	Vitamin K administration
	Antihistamines use
	Flumazenil use
	Naloxone use
	Antiemetic administration (for acute dyspepsia / nausea / vomiting)
	Haloperidol use
	Abrupt medication stop
Medication levels	Digoxin levels >2 ng/mL
	Carbamazepine levels >13 mcg/ml
Laboratory tests	Clostridioides difficile – positive stool
	Serum glucose <50 mg/dL
	Serum glucose >110 mg/dL
	INR > 5
	Haemoglobin or haematocrit decrease >25% / Acute bleeding
	Rising blood urea nitrogen or serum creatinine >2 times baseline
	Estimated glomerular filtration rate <35 mL/min/1.73 m2
	K > 6.0 mEq/L
	K < 2.9 mEq/L
	Na < 130 mEq/L
	ALT >80 U/L and/or AST > 84 U/L
	ALP > 350 U/L and/or total bilirubin >4 mg/dL
	CPK > 269 U/L
	TSH < 0.34 μUI/L or fT4 > 12 μg/dL
	White blood cells <3,000/μl
Emergency department	Emergency department visit within 48 h
	Time in emergency department >6 h
	Readmission within 30 days

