In detail, we will evaluate alert diagnoses: unexpected clinical manifestations occurring during the admission and that might be related or unrelated to the use (or lack of use) of a certain medication. We will also evaluate previously defined altered laboratory tests, according to reference laboratory and literature review. Finally, we will evaluate alert drugs: medications known to be used to correct an alteration produced by a first medication (e.g., naloxone to reverse opioid overdose). All triggers will be further reviewed to discern if they are clearly independent from clinical manifestations related to the patients’ condition. Causality will be then assessed using the 10-point Naranjo Scale (33). The severity of the event will be classified using a modified Hartwig and Siegel scale (34), ranging from trivial (event does not require additional treatment and as no sequalae) to fatal. Avoidability of the event will be assessed using a modified Schumock and Thornton questionnaire (35). Each potential ADE/ADWE form will be evaluated by the blinded members of the ADE/ADWE Adjudication Committee, consisting of a geriatrician and a clinical pharmacist not directly involved in the retrospective review process. In the case of disagreement, additional review by another blinded geriatrician/clinical pharmacist pair of evaluators will be requested. Also, 90 days post-discharge (post-discharge assessment), both experimental and control phase participants will be re-evaluated for quantitative polypharmacy, PROMs, unplanned health care utilization (acute hospital admission, emergency claims), and mortality.

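### ADEs and ADWEs are adjudicated event by event but compared by chi-squared as categorical variables, which uses neither repeat events nor time at risk (minor)

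*Protocol article*

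**What the plan says.** The Data analysis section names one test for these events: "the chi-squared test will be used to compare polypharmacy, hyperpolypharmacy, ADEs, ADWEs, and other categorical variables". The Design section adds: "The unit of analysis will be the patient".

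Under Participant timeline and data collection, the data are built event by event. Triggers from Table 2 are reviewed, causality, severity and avoidability are rated, and "Each potential ADE/ADWE form will be evaluated by the blinded members of the ADE/ADWE Adjudication Committee". The review period runs "from enrolment to index hospital discharge, or 30 days post recruitment, whatever comes first". The Study setting section reports: "The average length of stay per patient is around 30 days".

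The Data analysis section also plans a generalised linear mixed model for time and cluster, without naming its outcomes. It declares all secondary outcomes, which include ADEs and ADWEs, exploratory and not powered. No count or rate analysis of these events is named.

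**The concern.** With the patient as the unit and the event as a category, a patient with three adjudicated ADEs counts the same as a patient with one. A fall from three to one counts as no change. As events become common, the any/none scale saturates and loses contrast.

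Time at risk is a second issue. Stays average about 30 days and observation is capped at 30, so patients discharged early are observed for less time. Chi-squared takes no account of this. If stay differs between phases, the comparison mixes event risk with time observed.

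Third, a chi-squared test of pooled control against pooled intervention patients ignores ward and calendar period, which are built into a stepped wedge.

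At stake is how much the trial can say about drug-related harm, which its Objectives list among the safety effects to be evaluated.

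**Working it through.** **Layout.** Five wards, baseline plus five steps and 10 patients per cell (Sample size and recruitment; Figure 1 caption) give 5 × 6 × 10 = 300. Intervention cells are 5 + 4 + 3 + 2 + 1 = 15, so the split is 150 control and 150 intervention. This reproduces the stated 300.

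**Stated power.** The 75% belongs to the number of medications ("taking a baseline mean drugs of 8.81 and expected decrease of 1.31"). It cannot be checked without a standard deviation and says nothing about ADEs.

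**Calendar time.** Control cells in periods 1 to 6 number 5, 4, 3, 2, 1, 0; intervention cells number 0, 1, 2, 3, 4, 5. The mean period is 35/15 = 2.33 for control patients and 70/15 = 4.67 for intervention patients. A pooled test therefore compares earlier with later patients.

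**Time at risk (illustration).** At an assumed constant rate of 1.0 event per 30 days, the chance of any event is 1 − exp(−1.0) = 63% over 30 days and 1 − exp(−0.5) = 39% over 15 days, with no difference in underlying rate.

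**Power: assumptions.** The protocol gives no ADE rate, overdispersion or expected effect. Assumed ranges: control mean m from 0.1 to 2 events per patient, rate ratio R from 0.6 to 0.8, negative binomial dispersion k from 0 (Poisson) to 2. The protocol sets significance "with statistical significance at *p* < 0.05"; two-sided testing is assumed. Ward and period are ignored for both methods.

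- Any/none: p = 1 − exp(−m) for Poisson, or 1 − (1 + km)^(−1/k). Power = Φ[(|p0 − p1| − 1.96·SE0)/SE1], with SE0 pooled and SE1 unpooled.
- Count: SE² of the log rate ratio = (1/150)(1/m + 1/(mR) + 2k). Power = Φ(|ln R|/SE − 1.96).

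*Example 1: m = 1.0, R = 0.6, Poisson.* p0 = 0.632, p1 = 0.451, SE0 = 0.0575, SE1 = 0.0566, giving Φ(1.20) = 89%. Count: SE² = (1 + 1.667)/150 = 0.0178, SE = 0.133, giving Φ(0.511/0.133 − 1.96) = 97%.

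*Example 2: m = 1.0, R = 0.7, k = 1.* p0 = 0.500, p1 = 0.412, giving 33%. Count: SE² = (1 + 1.429 + 2)/150 = 0.0295, SE = 0.172, giving Φ(0.357/0.172 − 1.96) = 55%.

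Count power minus any/none power over the full grid:

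| Control mean per patient | Difference (points) |
|---|---|
| 0.1 | 0 to 1 |
| 0.2 | 1 to 5 |
| 0.3 | 2 to 8 |
| 0.5 | 4 to 15 |
| 1.0 | 8 to 27 |
| 1.5 to 2.0 | 6 to 40 |

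**With ward and period in both models.** A simulation (400 replicates per setting, R = 0.6, Monte Carlo standard error at most 2.5 points) gave, for any/none against count, 28% v 33% at mean 0.5 and 42% v 61% at mean 1.0 (Poisson). With overdispersion 1 the figures were 17% v 20% and 21% v 39%. So adjusting the any/none analysis for ward and period does not recover the repeat-event information. This simulation had no true ward or period effects and did not model varying observation time, so it does not test the offset.

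**A setting where the sign reverses.** Suppose the intervention changes only whether a patient has any event (30% v 18%), with 1 + Poisson(0.5) events among those affected. In 6,000 simulated trials, chi-squared had 69% power and the count analysis 57%.

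**The case against.** The strongest reply is that the protocol declares these outcomes exploratory and unpowered. That stands: no confirmatory conclusion depends on the choice, and the point is minor for that reason.

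Second, the protocol never says any versus none. That also stands: it is an inference, and a grouped count would fit the text. Pearson chi-squared on a grouped count would still ignore the order of the groups and the time at risk. The mixed model could in principle cover ADEs, but the only test the text assigns to them is chi-squared.

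Third, the proportion of patients with an event is a recognised, readable safety measure, and it is robust to double counting. Table 2 has overlapping triggers, such as acute kidney injury, rising creatinine and low eGFR, or delirium, lethargy and haloperidol use. The article does not say how they are merged into one event. This stands in part: counts need a merging rule first, and the proportion should stay in the report.

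A reader might infer a definite loss, say 5 to 20 points, whenever events are not rare. The documents do not support this. They give no rate, dispersion or effect; the computed range is about 0 to 40 points, and the sign can reverse.

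**Conclusion.** The point holds as a minor, inexpensive improvement. On the natural reading, the named test discards repeat events and time at risk that the trial will already have recorded, and it does not account for ward or calendar period.

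The cost in power depends on assumptions the documents do not settle. Under a proportional rate reduction (rate ratio 0.6 to 0.8) it is negligible at about 0.1 events per patient and material at 0.5 to 1.0. Under an effect on first occurrence only, chi-squared is the better test.

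A reader might go further and conclude that the safety findings would be invalid, or that the trial is underpowered because of this choice. Neither follows: the outcomes are exploratory, and the protocol makes no power claim for them.

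**What to change.** In the Data analysis section, take ADEs and ADWEs out of the chi-squared list. Analyse the number of adjudicated ADEs per patient, and separately of ADWEs, with a negative binomial or overdispersed Poisson model. Include ward and period terms and the log of days observed as the offset, and report rate ratios with 95% confidence intervals. State that triggers arising from the same clinical episode count as one event. Report alongside it the proportion of patients with at least one event, by phase.

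The cost is wording and a merging rule for adjudication; event-level data are already planned. The downside is that counts are sensitive to how overlapping triggers are merged and to a few patients with many events. The overdispersion term and the any-event proportion limit the second risk.

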**Figure 1 fig1:**
[figure not shown]
Stepped-wedge trial design. C, cluster; 0, control; 1, intervention. Each square includes 10 patients.

The computer-generated stepwise randomization of clusters will be carried out with the statistical software R with a randomization seed 184.

For the identification of barriers and enablers for the implementation, we will follow qualitative analysis combining techniques of semi-structured interviews and focal groups.

Trial registration (clinical trial number): NCT07015112 (June 10, 2025).

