### Participant timeline and data collection

Enrolled patients will be evaluated upon admission for the variables detailed in Table 1 (baseline assessment) and undergo medication review (see “Interventions”). Since the planned intervention will be performed upon hospital admission, we expect nearly total retention. In detail, a trained clinical pharmacist and a geriatrician will perform an evaluation on demographic data, a brief multidimensional geriatric assessment, including the evaluation of the frailty, and data on quantitative/qualitative polypharmacy.

For the intervention phase, PROMs will be assessed upon admission through an interview conducted by a trained clinical pharmacist (see Table 1). Figure 3 summarizes the timeline for the intervention phase.

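### The described effect model does not name the admission medication count, which every patient has before the review and which could add power at no data cost

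*Protocol article*

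**What the plan says.** **Outcome.** Under Outcomes: "The primary outcome of the study is the mean number of medications per patient". That sentence gives no time point.

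**Model.** Under Data analysis: "We will perform a generalized lineal model with mixed effects for (individual) time and cluster". The sentence names time and cluster. It names neither the admission count nor the intervention term. The same section plans a Student's t-test for mean medications, which is unadjusted. It also plans stratification by frailty and age group where appropriate, and a separate multivariable analysis of what determines the decrease in medications at discharge. Significance is set "with statistical significance at *p* < 0.05", with no sidedness given.

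**Data available.** Under Participant timeline and data collection: "Enrolled patients will be evaluated upon admission for the variables detailed in Table 1 (baseline assessment", after which patients undergo the medication review. Table 1 includes quantitative polypharmacy and defines how long-term medications are summed. The count therefore exists before the review in both control and intervention patients.

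**Sample size.** The calculation is described as "considering 5 clusters, a size of each cluster *N* = 10 and five times of measurement after baseline", "taking a baseline mean drugs of 8.81 and expected decrease of 1.31", with an ICC of 0.2. It concludes that "a sample size of 300 subjects will provide a power of 75" per cent. The Figure 1 legend adds: "Each square includes 10 patients".

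**The concern.** Control and intervention patients are different people, and the outcome is a count that should depend substantially on what each patient was taking on arrival. If the admission count is left out, the variation it could explain stays in the error term. The trial accepted 75% power to remain feasible, and its Discussion warns that the assumed effect may be too large, so precision that needs no new data is worth having.

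The second issue is imbalance. The trial is open-label and patients are selected on admission, when the ward's phase can be known. With 10 patients per ward-period, admission polypharmacy can differ between phases by chance or through selection. Ward and period terms remove stable ward differences and secular trends, but not patient-level differences within those cells.

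**Working it through.** **Inputs from the article.** 5 wards, 6 periods (1 baseline + 5 steps), 10 patients per ward-period, difference 1.31, ICC 0.2, significance level 0.05 (taken as two-sided), stated power 75%. Total: 5 × 6 × 10 = 300, which agrees.

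**Inputs not in the article.** The SD of the count, and the within-ward correlation r between admission and outcome counts. The SD is solved from the stated power. r is an assumption, shown from 0.3 to 0.8.

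**Variance formula.** Hussey-Hughes for a cross-sectional stepped wedge:

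Var = I·s²·(s² + T·τ²) / [(I·U − W)·s² + (U² + I·T·U − T·W − I·V)·τ²]

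Here I = 5, T = 6, s² is the within-ward variance divided by 10, and τ² is the ward variance. With one ward crossing at each step:

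- U = 5 + 4 + 3 + 2 + 1 = 15
- W = 0 + 1 + 4 + 9 + 16 + 25 = 55
- V = 25 + 16 + 9 + 4 + 1 = 55
- I·U − W = 75 − 55 = 20
- U² + I·T·U − T·W − I·V = 225 + 450 − 330 − 275 = 70

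**Step 1: the stated 75%.** In units of total SD, τ² = 0.2 and s² = 0.8/10 = 0.08.

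Var = 5 × 0.08 × (0.08 + 1.2) / (20 × 0.08 + 70 × 0.2) = 0.512 / 15.6 = 0.03282, so SE/SD = 0.1812.

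75% power needs 1.31/SE = 1.960 + 0.674 = 2.634, so SE = 0.497 and SD = 0.497/0.1812 = 2.74. The 75% cannot be confirmed independently because no SD is given: an SD of 2.5 would give 82%, 3.0 gives 67% and 3.5 gives 54%. The Woertman design effect leads to the same 2.74.

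**Step 2: add the admission count.** Multiply the within-ward variance by (1 − r²) and leave the ward variance unchanged. At r = 0.5, s² = 0.08 × 0.75 = 0.06:

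Var = 5 × 0.06 × (0.06 + 1.2) / (20 × 0.06 + 14) = 0.378 / 15.2 = 0.02487, so SE/SD = 0.1577 and SE = 0.433.

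Power = Φ(1.31/0.433 − 1.96) = Φ(1.07) = 85.7%.

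| r | Power | Gain (points) |
|---|---|---|
| 0 | 75.0% | – |
| 0.3 | 78.7% | 3.7 |
| 0.4 | 81.7% | 6.7 |
| 0.5 | 85.7% | 10.7 |
| 0.6 | 90.5% | 15.5 |
| 0.7 | 95.5% | 20.5 |
| 0.8 | 99.1% | 24.1 |

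**Step 3: sensitivity.**

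- Reducing the ward variance by the same factor changes power by less than 0.5 point.
- For r from 0.5 to 0.7, the gain is 9 to 16 points at SD 2.5, 12 to 24 at SD 3.0 and 12 to 28 at SD 3.5.
- With a t reference on 4 degrees of freedom, recalibrated to 75%, it is 10.1 to 19.7 points.
- Simulation with fixed ward and period effects (3,000 runs per r) gave 73% to 77% at r = 0.3, 73% to 85% at r = 0.5 and 72% to 94% at r = 0.7.

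**The case against.** The strongest objection is that the model sentence is a summary and not a specification. It omits the intervention term too, so silence on a covariate does not prove the covariate is excluded, and a fuller analysis plan may contain it. The reference to individual time could even mean repeated measures within patients, with the admission count entering as an observation. This stands as far as it goes: the omission is not proven. The article nevertheless describes the effect model by its terms, and as described the admission count is not among them.

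The related analyses do not fill the gap. Stratifying by frailty and age is not adjustment for the admission count, and the analysis of determinants of the decrease is separate from the effect estimate.

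Three stronger readings are tempting, and the article does not support them:

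- **That admission differences between phases are wholly unadjusted, so the estimate is biased.** Ward and period effects already remove ward-level and secular differences. Chance imbalance is reflected in the standard error and is not bias. Selective recruitment is possible, but nothing shows that it will occur, and one covariate would address it only in part.
- **That the sample size plans for a change while the model compares levels.** A mean of 8.81 and a decrease of 1.31 can simply be a control mean and a between-condition difference.
- **That the plan gives up a known 10 to 20 points of power, or that most between-patient variation is predictable from admission.** A gain of 10 to 20 points needs r of about 0.48 to 0.69. Correlations of 0.5 and 0.7 explain 25% and 49% of within-ward variance, which is not most of it.

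**Conclusion.** The point holds as a recommendation to name a covariate. The described model does not name the admission medication count, although it is measured before the review in every patient and is the obvious prognostic variable for this outcome. The benefit is conditional: about 4 points of power at r = 0.3, 11 at r = 0.5, 20 at r = 0.7 and 24 at r = 0.8. These figures rest on an SD of 2.74 inferred from the stated power, a two-sided 0.05 test and an assumed r. The true r will also depend on when the outcome count is taken (discharge or 90 days after it), which the outcome sentence does not fix. Reduced sensitivity to residual patient-level imbalance is a further benefit that was not quantified. The point does not establish that the planned estimate is biased or that the planned effect and model contradict each other.

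**What to change.** State the primary model as outcome count on intervention, period, ward and admission count of long-term medications (Table 1 definition), with the admission count as a fixed covariate. If individual time is meant to indicate repeated measures that already include the admission count, say so. Age and the frailty index are optional additions, since both are already collected. Settle this before any analysis, so that there is no later choice between adjusted and unadjusted results. The cost is one line of text, with no new data and no change to recruitment or care.
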